# A randomized controlled feasibility study to evaluate the effects of a goal-setting coaching intervention using feedback from an accelerometer on sedentary time in older people at risk of falls (SMART-MOVE): a study protocol

**DOI:** 10.1186/s40814-018-0366-5

**Published:** 2018-11-17

**Keywords:** Accelerometer, Falls, Health coaching, Older people, Sedentary behaviour

## Abstract

**Background:**

Sedentary behaviour and falls are important interrelated health issues in older people. One in three people aged 65 years and above fall at least once a year and sedentary behaviour has been identified as one of the risk factors for falls. Studies have shown that the duration of sedentary time increases with age. These dual problems need to be addressed effectively as the ageing population grows. Accelerometers enable accurate measurement of sedentary time. This study aims to establish the feasibility and effect of an individualized goal-setting health coaching intervention using feedback initially from an accelerometer and then pedometer over a period of 12 weeks (intervention) compared with providing a one-off advice through a brochure (control), on sedentary time in older people with a recent fall or at risk of one.

**Methods:**

A single-blinded randomized controlled feasibility trial involving 80 community-dwelling people aged 65 years and above will be conducted with 40 randomized to the intervention and another 40 to control. Primary outcomes will be the feasibility of the intervention and change in total sedentary time at 12 and 24 weeks. Secondary outcomes include a change in fear of falling based on the falls efficacy scale, gait speed, self-reported sedentary time, the proportion of fallers and number of falls. Four focus groups (two from each arm) will be conducted at the end of the study to evaluate the feasibility and effectiveness of this intervention. Feasibility findings will be primarily descriptive. Mean group differences will be examined using independent samples *t* test for normally distributed data and nonparametric tests (Kruskal-Wallis and Mann-Whitney *U*) for non-normally distributed data. Differences in frequency of variables will be compared using chi-square test. Analysis of variance (ANOVA) will be used to test the post-intervention difference between the two groups at 12 and 24 weeks.

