## Aims

The primary aim of this trial is to evaluate the feasibility and effect of a goal-setting health coaching intervention based on initial accelerometer and then pedometer feedback on total sedentary time for 12 weeks compared to one-off advice through a brochure in reducing sedentary behaviour in older people at high risk of falling according to the STEADI criteria (had a fall in last 12 months, feel unsteady when walking or standing, and/or worry about falling) [29].

The secondary aims are to compare the change in sedentary time based on the self-reported Measure of Older Adults' Sedentary Time (MOST) questionnaire [30], FES [31], change in gait speed, proportion of fallers and numbers of falls.

Evaluation of effects at 24 weeks will also occur to determine if the changes seen with the intervention compared to control is sustained at 24 weeks.

It is hypothesized that the intervention will be feasible with a 40% recruitment rate and an 80% retention rate will be achieved at 6 months. For adherence and acceptability, it is hypothesized that goal attainment scale of 0 (indicating goal achieved) for at least three goals will be achieved in 70% of participants (intervention group) and the intervention is acceptable in 70% of the participants. A further hypothesis is that the intervention is effective in reducing sedentary time and the benefits sustained at 24 weeks.

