### Statistical analyses

Feasibility findings will be primarily descriptive and used as a metric for improvement when compared to similar studies. We hypothesize that the intervention will be feasible among several improvement metrics including 40% or more recruitment rate and less than 20% attrition. This hypothesis is based on findings from earlier studies [13–16].

Descriptive analyses will be conducted using mean with standard deviation, median with interquartile range and frequency for baseline characteristics. These characteristics include age, gender, ethnicity, physical function, health status, quality of life and mental status. Mean group differences will be examined using independent samples *t* test for normally distributed data and nonparametric tests (Kruskal-Wallis and Mann-Whitney *U*) for non-normally distributed data. Differences in frequency of variables will be compared using chi-square test.

Analysis of variance (ANOVA) will be used to test the post-intervention difference at 12 and 24 weeks between the two groups. The covariates in the analysis will include baseline values of the dependent variable and any variable significantly different between groups at baseline. Group mean values for adherence variable at 12 and 24 weeks (retention rate, days the accelerometer and pedometer are worn) will be analysed by an independent *t* test. The data analysed will be based on the intention-to-treat analysis.

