### Power calculation

Sixty-four participants will be required to detect a 30 min/day reduction [15] in sedentary time (80% power, alpha 0.05) in the interventional group, assuming there is no change in the control arm. Therefore, the aim is to recruit 80 participants (40 in each arm) to allow for 20% attrition. The same number of male and female participants will be recruited.

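### Sedentary time is primary at both 12 and 24 weeks, but the plan sizes one test at alpha 0.05 and fixes no order between the visits

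*Protocol article*

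**What the plan says.** The Abstract (Methods) puts the two visits on an equal footing: "Primary outcomes will be the feasibility of the intervention and change in total sedentary time at 12 and 24 weeks". In the body, the sedentary-time paragraph under Primary outcomes names no visit, and Table 4 schedules the accelerometer at baseline, week 12 and week 24.

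The Aims link the primary aim to the 12-week intervention and add the later visit separately, "to determine if the changes seen with the intervention compared to control is sustained at 24 weeks". The efficacy hypothesis there is joint: a reduction in sedentary time, and persistence of the benefit at 24 weeks.

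Under Statistical analyses: "Analysis of variance (ANOVA) will be used to test the post-intervention difference at 12 and 24 weeks between the two groups". The baseline value of the outcome is a covariate. The section closes with "The data analysed will be based on the intention-to-treat analysis".

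The Power calculation reads: "Sixty-four participants will be required to detect a 30 min/day reduction [15] in sedentary time (80% power, alpha 0.05"). It assumes no change in the control arm and raises the number to 80 "to allow for 20% attrition". It does not say which visit the 64 refers to.

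**The concern.** The sections do not agree on what week 24 is for. In the Abstract it is a primary time point equal to week 12. In the Aims it is a check on durability. The sample size belongs to one comparison at one alpha, and nothing says which.

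As written, the trial could report a positive primary efficacy result from week 12 alone, from week 24 alone, or from both. Two chances of success at 5% each carry a false-positive risk above the 5% on which the sample size rests. A null result at week 12 with a nominally significant one at week 24 would be especially awkward. The Abstract would allow it as a primary success, whereas the Aims would see no earlier effect to sustain.

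**Working it through.** **Inputs from the documents.** Two primary time points (Abstract); a between-group test at each, with baseline as covariate (Statistical analyses); alpha 0.05, power 80%, 30 min/day, 64 evaluable, 20% attrition, 80 recruited (Power calculation); 1:1 allocation (Study design).

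**Inputs assumed.** Two-sided tests, since sidedness is not stated. The correlation ρ between the week-12 and week-24 test statistics is not given and is varied below.

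**The plan's own figure.** 64 / (1 − 0.20) = 80, which agrees. The 64 itself cannot be rebuilt because no SD is stated. Solving backwards with 32 per arm on the normal approximation: SD = 30 / [(1.960 + 0.842) × √(2/32)] = 30 / (2.802 × 0.25) = 42.8 min/day. This implied SD is used only to price an alpha split.

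**False-positive rate if either visit counts.** With no effect at either visit, the rate is 1 − P(|Z₁| < 1.96 and |Z₂| < 1.96), with (Z₁, Z₂) bivariate normal with correlation ρ.

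| ρ | Chance of at least one false positive |
|---|---|
| 0 | 9.75% (= 1 − 0.95²) |
| 0.5 | 9.1% |
| 0.7 | 8.35% |
| 0.8 | 7.8% |
| 0.9 | 7.0% |

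This is 1.4 to 1.95 times the nominal 5% (7.0/5 and 9.75/5).

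**Effect of baseline adjustment.** If all three visits correlate equally at r, adjusting for baseline leaves a week-12 to week-24 correlation of (r − r²)/(1 − r²). For r = 0.5 this is 0.33 and the rate is 9.5%. For r = 0.8 it is 0.44 and the rate is 9.2%. Equal correlation is again an assumption.

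**Rules that would contain the error.**
- Fixed order, week 12 then week 24, each at 5%: 5%. With no effect at week 12, any false claim must first pass that 5% test. With a real effect at week 12 and none at week 24, the only false claim is the week-24 test at 5%.
- Both must succeed: at most 5%. With no effect at either visit it is 2 × 5% − 9.07% = 0.9% at ρ = 0.5.
- Alpha split at 0.025 each: at most 4.9% (1 − 0.975² = 0.0494). With the implied SD, power per visit at 32 per arm falls from 80% to Φ(2.802 − 2.241) = 71%. Restoring 80% needs 39 per arm, so 78 evaluable and 78/0.80 = 97.5, that is 98 recruited.

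The fixed order is the only one of the three that keeps the planned power at week 12, leaves the sample size alone and allows a claim from week 12 by itself.

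**The case against.** The strongest reply is that an order is already implied. The Aims treat week 24 as a question of persistence, and the joint hypothesis would not be met by a week-24 result alone. The Discussion ties the 30-minute target to the 12-week intervention. The equal listing comes from a condensed abstract, and this is a feasibility study. Much of that stands: the fault is an order that is suggested and not fixed, and the remedy is small. It does not remove the point. The Abstract states the primary outcomes, the Statistical analyses section tests both visits without ranking them, and the trial sets and powers an efficacy hypothesis. Only the feasibility findings are described as mainly descriptive.

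Two stronger readings are not supported.

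- **Missing data.** A reader might infer that the ANOVA discards participants lost to follow-up and so breaks the intention-to-treat statement. An ANOVA at each visit without imputation would use only those measured, but the article gives no missing-data rule, and such a rule may properly sit in an analysis plan that is not shown. The 64 of 80 is an attrition allowance in the sample size and does not define the analysed set. Separate models are the likelier reading of the text, but a repeated-measures ANOVA is not excluded. Missing data also plays no part in the false-positive figure.
- **Size.** A reader might call the error doubled, or quote a narrow 8–9%. Doubling overstates even the extreme of 1.95 times. A narrow band needs correlations that the documents do not give. Nor does the text say that each visit is tested at 5%: alpha 0.05 appears only in the Power calculation.

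**Conclusion.** The point holds as a matter of multiplicity and of internal consistency. Two visits are primary, one alpha is planned for, and the rule joining them is left open. If a win at either visit counts, the false-positive rate is about 7.0% to 9.75% against the planned 5%. This assumes two-sided 5% tests at each visit and a correlation between 0.9 and 0. With both tests at 5%, the rate stays at or below 5% only under a fixed order or a both-must-succeed rule, which the Aims suggest without fixing. It is not shown that intention-to-treat is unmet. The correction is worth making because it is cheap and follows the reasoning already in the Aims.

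**What to change.** 1. State in the Abstract, Primary outcomes and Power calculation that the week-12 group difference in total sedentary time is the single primary efficacy contrast, and that the sample size refers to it.
2. State that week 24 is tested for a sustained effect, at 5%, only if week 12 is significant. Otherwise report its estimate and confidence interval without a claim.
3. As a secondary improvement, take both contrasts from one repeated-measures mixed model with arm by visit, the baseline value, and sex as the stratification factor, using every randomised participant with any follow-up measurement. Someone seen at only one visit then still contributes. This serves the stated intention-to-treat aim better than an ANOVA at each visit, although it cannot recover those with no follow-up, and it relies on data being missing at random given what was observed.

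Items 1 and 2 are changes of wording and leave the 80 participants unchanged. Their price is that week 24 cannot support an efficacy claim by itself, a role the Aims do not give it. Item 3 costs more, since it changes the named method, and the first two do not depend on it.

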**Discussion:**

The trial will address a key gap in evidence about sedentary behaviour and falls amongst older people and will evaluate the feasibility of an intervention that could be implemented within the primary health care settings.

**Trial registration:**

Australian New Zealand Clinical Trials Registry 12617001186347, Registered 11 August 2017.

## Background

Falls are common among older people. It is estimated that about 30% of people aged 65 years or older fall at least once a year [1]. In Australia, this approximates to one million people annually [2]. Falls are a major contributor to injuries, disability and premature death, substantially impacting on the health and independence of older people [3]. The economic costs of falls are huge, with an annual direct medical cost of $30 billion in the USA [4]. Therefore, the prevention of falls among older people must be addressed urgently because the burden of this problem will only increase if no intervention is undertaken.

Falls are associated with many risk factors, and sedentary behaviour is one of them [5]. Sedentary behaviour refers to low-energy expending behaviour undertaken while sitting or lying down when awake [6]. Older people have been found to be sedentary more than 70% of their time, i.e., 8–10 h of their waking day, and this increases linearly with age [7]. A meta-analysis of eight observational studies has reported that sedentary behaviour was associated with an increased risk of falls [8]. Lower extremity muscle weakness and balance impairment may be mediating factors between sedentary behaviour and falls [8].

Furthermore, there is also concern that sedentary behaviour increases after older people have had falls [9]. Fear of falling and slow gait speed are associated with an increased risk of falls. Low falls efficacy scale (FES), a measure of fear of falling, is associated with an increased risk of subsequent falls, a decline in activities of daily living and reduced quality of life [3]. The association between gait speed and falls is non-linear, with a higher risk of falls outdoor among faster speed walkers, and falls indoor among slow-speed walkers [10].

There is a growing body of evidence that has shown multifactorial interventions including exercise programs especially those that improve balance and strength training, gait training, medication reviews, home risk modifications and education are effective to prevent falls in community-dwelling older people [11]. Many intervention studies aimed at increasing physical activity have been used to reduce falls [12]. However, no study has evaluated whether the reduction in sedentary behaviour can influence falls risk and only a few have examined effective ways to reduce sedentary behaviour among older people [13–16]. Moreover, standardized supervised exercise interventions do not necessarily reduce sedentary behaviour in the older population [17]. Increasing physical activity does not always result in reduced sedentary time. Therefore, reducing sedentary behaviour is a distinct domain and has to be addressed separately from increasing physical activity [18].

To date, there is only one randomized controlled trial comparing reducing sedentary behaviour (“Sit Less” group) and increasing moderate to vigorous physical activity (MVPA) (“Get Active” group) among 38 community-dwelling older people aged > 60 years, for a period of 12 weeks [19]. The goal for the “Sit Less” group was to reduce sedentary time by 60 min each day while the “Get Active” group was to reach 150 min of MVPA each week. Both groups received a combination of individual, face-to-face and phone consultations with an exercise physiologist. Sedentary time did not change in either group but the “Sit Less” group improved their short physical performance battery (SPPB) score by 0.5 ± 0.3.

Accelerometers are devices used to measure the acceleration of movement that can be categorized into different intensities of activity. One such accelerometer, ActivPAL, is useful for measuring free-living sedentary behaviour [20]. Self-monitoring technologies such as pedometers are increasingly used as motivational tools to increase physical activity. Pedometers are simple and inexpensive body-worn movement sensors. Pedometers have been found to be associated with improvement in physical activity [21]. Several studies have demonstrated that pedometers can successfully increase physical activity in older people [22–24]. Therefore, the use of pedometers may have a role in reducing sedentary behaviour by providing immediate and objective feedback.

Health coaching is the practice of health education and health promotion within a coaching context, to enhance the well-being of individuals and to facilitate the achievement of their health-related goals [25]. In health coaching, a coach helps the participant to achieve their health-related goals by facilitating the learning process. Health coaching has been found to be an effective method to support behaviour change amongst older people. Health coaching based on behaviour change theories such as self-determination theory (SDT) has a strong evidence of efficacy [26]. SDT targets perceptions of autonomy, competence and relatedness to increase autonomous motivation, that is volitional and internal rather than external [27]. Using health coaching to reduce sedentary duration in older people is still a new approach. The Coventry, Aberdeen and London—Refined (CALO-RE) taxonomy is a tool to specify the content of behavioural change interventions [28]. Nine domains in this taxonomy are useful in designing health coaching interventions. Each domain describes a technique that is used in influencing an aspect of participants’ behaviour. These domains include shaping knowledge about health consequences, goal-setting (behaviour), goal-setting (outcome), feedback on behaviour, action planning, barrier identification or problem-solving, use of follow-up prompts, review of goals and relapse prevention.

Four small pre- and post-intervention studies in community-dwelling older people have been conducted using health coaching to reduce sedentary behaviour [13–16]. These studies reported reductions in objectively measured sedentary time ranging between 24 and 51 min per day. However, the main limitation with these studies was a short duration of intervention (between 1 and 14 days) [13, 15, 16]. To date, no studies on reducing sedentary behaviour have targeted older people with a history of falls or falls risk. Therefore, an individualized goal-setting intervention has been developed to reduce sedentary behaviour by using health coaching based on initial accelerometer and then pedometer over 12 weeks.

## Aims

The primary aim of this trial is to evaluate the feasibility and effect of a goal-setting health coaching intervention based on initial accelerometer and then pedometer feedback on total sedentary time for 12 weeks compared to one-off advice through a brochure in reducing sedentary behaviour in older people at high risk of falling according to the STEADI criteria (had a fall in last 12 months, feel unsteady when walking or standing, and/or worry about falling) [29].

The secondary aims are to compare the change in sedentary time based on the self-reported Measure of Older Adults' Sedentary Time (MOST) questionnaire [30], FES [31], change in gait speed, proportion of fallers and numbers of falls.

Evaluation of effects at 24 weeks will also occur to determine if the changes seen with the intervention compared to control is sustained at 24 weeks.

It is hypothesized that the intervention will be feasible with a 40% recruitment rate and an 80% retention rate will be achieved at 6 months. For adherence and acceptability, it is hypothesized that goal attainment scale of 0 (indicating goal achieved) for at least three goals will be achieved in 70% of participants (intervention group) and the intervention is acceptable in 70% of the participants. A further hypothesis is that the intervention is effective in reducing sedentary time and the benefits sustained at 24 weeks.

## Methods/design

This trial has been designed in accordance with the CONsolidated Standards of Reporting Trials (CONSORT) statement [32, 33] and is reported according to the Standard Protocol Items: Recommendations for Interventional Trials (SPIRIT) statement [34] and with reference to the Template for Intervention Description and Replication (TIDieR) checklist (see Table 1) [35].

**Table 1 Tab1:** Intervention description using the Template for Intervention Description and Replication (TiDieR) checklist

1. Brief name	SMART-MOVE Specific, Measurable, Attainable, Relevant and Time-bound (SMART) Goal-setting coaching and accelerometer feedback to reduce older people’s sedentary time (MOVE)
2. Why	Excess time in sedentary behaviour is a prevalent health risk in the older population. Even amongst those who achieved the recommended requirement for physical activity, sedentary behaviour is considered detrimental and increasingly recognized as a health risk independent of physical activity. It is associated with adverse outcomes, such as falls, which is in turn a risk factor for fragility fractures. There is an urgent need to address this issue as the number of older people is expected to increase due to population ageing. Few studies have evaluated interventions to increase physical activity levels in older people who are at risk of falls. The coaching intervention is based on self-determination theory on modification of behaviour.
3. What—materials	Participants will receive: • The ‘Choose Health: Be Active’ booklet developed by the Australian Government in collaboration with Department of Veterans’ Affairs and Department of Health and Aging to help older Australians achieve sufficient physical activity for good health as they age. • An accelerometer to record sedentary behaviour for a week (at week 1, 12 and 24). • A SMART goal-setting booklet will be given to participants in the intervention group. • A pedometer to measure daily step counts.
4. What—procedures	Face-to-face coaching with goal setting will occur after accelerometer reading is available at the start of the study and then at week 6. Subsequently, telephone interviews will occur fortnightly on four occasions (week 2, 4, 8 and 10) to identify barriers and assist participants to achieve their physical activity goals.
5. Who provided	Two researchers with professional backgrounds in medicine and nursing will deliver the intervention.
6. How	The intervention will be tailored to suit the participant daily activities. SMART (specific, measurable, attainable, relevant, time-bound) goals will be set. At the first face-to-face meeting, participants will set three goals to reduce sedentary behaviour. One goal will be incrementally introduced every 2 weeks so that by week 6, the participant will be working on three goals. At the second face-to-face meeting, the participant will set another three goals that will be added incrementally every fortnight. Participants in the intervention arm will be provided with information about their duration of time spent upright (accelerometer) and total number of steps (pedometer) taken each day. Goals are set to increase their time spent upright and total number of steps taken. Participants will calculate the mean daily steps over 7 days and increase by 200 steps from the mean per week as a goal. They will also be encouraged to attend falls prevention classes if they have not participated in one in the preceding 12 months.
7. Where	The intervention will be delivered to community-dwelling older people who had at least one fall in the last 12 months or are at risk of one. It will be delivered at Adelaide G-TRAC Centre or The Queen Elizabeth Hospital.
8. When and how much	The face-to-face assessment, goal setting and health-coaching will occur at the beginning of the intervention period and will last approximately 2 h. An accelerometer will be worn for one week before this face-to-face coaching. Phone coaching will occur for up to 15 min fortnightly when there is no face-to-face coaching. At week 6, a second face-to-face coaching will be conducted where goals will be reviewed and additional goals set.
9. Tailoring	The recommended physical activity plan will be tailored to individual needs based on participants’ goals, baseline levels, preferences and physical ability.

